## Abstract

Waist girth (WG) represents a quick, simple, and inexpensive tool that correlates with excess of fat mass in humans; however, this measurement does not provide information on body composition. The evaluation of body composition is one of the main components in the assessment of nutritional status. Indeed, the use of anthropometry-based equations to estimate body fat and fat-free mass is a frequent strategy. Considering the lack of validation in the Colombian population, the aim of this research study (the F20 Project) is to externally validate WG-based equations (e.g., relative fat mass), and also to develop and validate new models that include WG to estimate body composition in Colombian adults compared to DXA. This cross-sectional study will be carried out following the guidelines for Strengthening the Reporting of Observational Studies in Epidemiology–Nutritional Epidemiology (STROBE–nut). Using stratified probabilistic sampling, the study population will be adults with different levels of physical activity residing in Medellín and its metropolitan area. The results of this study will not only validate the estimation performance of the current WG-based equations, but they will also develop new equations to estimate body composition in the Colombian population. This will improve professional practice in health, exercise, and sports sciences (ClinicalTrials.gov ID #NCT05450588).

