### 1.2. Objectives

The use of equations to estimate body composition is a frequent strategy since it represents a doubly indirect method with a good correlation to the methods mentioned above. However, this leads to the question of whether current WG-based equations are valid for estimating fat mass and fat-free mass in the Colombian population with different levels of physical activity? On the other hand, would it be advantageous to develop new models to obtain a specific equation for the Colombian population? Thus, the aim of this study will be twofold: (i) externally validate the current WG-based equations to estimate fat mass and fat-free mass as compared with DXA, and (ii) develop new models to estimate fat mass and fat-free mass using the WG as a predictive variable, and subsequently validate the new equations in the Colombian population with different levels of physical activity.

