### 2.3. Participants

The study population will be healthy, male and female residents of Medellín and the nearby municipalities that make up its metropolitan area (the Andean Region of Colombia), who exhibit different levels of physical activity. The sample of the sedentary population will be obtained through an open call to both students and administrative personnel at Universidad CES. The sample of the physically active population will be obtained from the collaboration agreement between DBSS International and Smart Fit Colombia, for which a sample of personalized trainers working in Medellín and its metropolitan area will be used. Finally, the sample of professional athletes will be obtained by taking advantage of the interinstitutional relations of the Research Division of DBSS International and the IPS ARTHROS—Physiotherapy and Exercise Center with clubs and sports entities in Antioquia.

In order to comply with the objectives of this research, the following will be taken into consideration as inclusion criteria: (i) +18 years old (under 60 years); (ii) residing in the city of Medellín or nearby municipalities of the metropolitan area; (iii) low, moderate, and high categories, according to the IPAQ-SF questionnaire [44] for sedentary, physically active, and athletes, respectively. In addition, athletes will need to demonstrate previous experience in sports events (>1 year) and current affiliation with a club team participating in league games or sanctioned tournaments; (iv) signed, informed consent to submit to the anthropometric and DXA measurements. The following participants will be excluded: (i) those individuals diagnosed with a disease and/or a special condition that limits exposure to radiation emitted by DXA; (ii) adults over 60 years of age; (iii) pregnant women; (iv) athletes with injuries; and (v) people with implants or prostheses. All procedures will be developed in accordance with the latest version of the Declaration of Helsinki [45]. The study protocol has been approved by the Research and Innovation Committee at the University CES (Acta0031Proy115TG) and registered with ClinicalTrials.gov (ID #NCT05450588).

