### 2.7. Study Size

According to Knofczynski and Mundfrom [53], to obtain (at least) a coefficient of determination (R^2^) of 0.5 with an excellent level of prediction using 3 independent variables, a total of 130 participants will be needed. Stratified probability sampling techniques will be used. Thus, the total number of participants will be divided into three strata following optimal allocation methods. A fixed cost has been assigned for each stratum (sedentary persons, C1; physically active subjects, C2; and athletes, C3, given that C3 > C2 > C1) to calculate the sample size of each population using Lagrange multipliers, given by the expression:(1)$$nh=n\;\frac{NhSh/\surd Ch}{\sum_{h=1}^{L}NhSh/\surd Ch},\;h=1,\;2,\;\ldots ,\;L$$
where, the values of *n_h_* correspond to the sample units for each stratum, *N_h_* is the maximum number of participants allowed, *C_h_* is the constant cost in all strata, *L* is the number of strata, and *S_h_* is the population quasi-variance of stratum *h*. The values obtained for the sedentary group are *n* = 54; for the physically active population group, *n* = 43; and for the athlete group, *n* = 33. To validate the new equation, the development/validation ratio will be 70/30 over the number of subjects participating in the study.

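### The sample is labelled a stratified probability sample but is recruited by open call and institutional contacts, so design-based inference to the Colombian population is not supported

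*Protocol article*

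**What the plan says.** The Abstract describes the design thus: "Using stratified probabilistic sampling, the study population will be adults with different levels of physical activity residing in Medellín and its metropolitan area". Section 2.7 repeats the label, "Stratified probability sampling techniques will be used", and then gives an optimal-allocation formula that yields 54 sedentary, 43 physically active and 33 athlete participants.

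Section 2.3 describes how people actually enter:

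- Sedentary: "The sample of the sedentary population will be obtained through an open call to both students and administrative personnel at Universidad CES".
- Physically active: an agreement with one gym chain, "for which a sample of personalized trainers working in Medellín and its metropolitan area will be used".
- Athletes: "the sample of professional athletes will be obtained by taking advantage of the interinstitutional relations" with clubs and sports bodies in Antioquia.

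The same section ties the low, moderate and high IPAQ-SF categories to these three groups in that order. Athletes must also have more than a year of competition and a current club affiliation. Eligibility is limited to healthy adults from 18 to under 60 in Medellín and nearby municipalities.

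Section 1.2 sets the second aim to develop new equations and "subsequently validate the new equations in the Colombian population with different levels of physical activity". The Conclusions foresee use of the equations across the country's health system. Section 2.8 lists physical activity level among the candidate predictors of fat mass. Section 2.6 (Bias) deals with measurement error only.

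**The concern.** A probability sample needs a frame from which people are drawn with known, non-zero probabilities. That property is what lets a study generalise from its design alone, without a model for who took part. An open call cannot supply it, because those who answer select themselves. The protocol therefore claims a property that its recruitment section rules out.

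Two things are at stake. The first is the reach of the validation: a reader who trusts the label will take the reported bias, RMSE and concordance as estimates for Colombian adults. The second is the new equation. If activity level is selected as a predictor, its coefficient will carry whatever else differs between university volunteers, personal trainers and club athletes. The planned validation has no means of detecting that.

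**Working it through.** **1. The label against the recruitment.** Shares are n/130.

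| Stratum | IPAQ-SF category | Route of entry (2.3) | n (2.7) | Share | Selection probability known? |
|---|---|---|---|---|---|
| Sedentary | low | open call, one university | 54 | 41.5% | no, self-selected |
| Physically active | moderate | trainers, one gym-chain agreement | 43 | 33.1% | none described |
| Athletes | high, plus club and competition criteria | institutional links with clubs | 33 | 25.4% | none described |

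The sizes add up: 54 + 43 + 33 = 130. The largest stratum contradicts the label outright. For the other two, no list or random draw is mentioned.

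**2. What the formula does.** Section 2.7 sets n_h = n · (N_h S_h/√C_h) / Σ(N_h S_h/√C_h). It decides how many people each stratum contributes, not which people. It also defines N_h as a cap on participants rather than the size of the stratum in the population, so the shares need not reflect population shares.

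The values of N_h, S_h and C_h are not given, so 54/43/33 cannot be recomputed. A consistency check is possible. If N_h S_h were equal across strata, n_h would be proportional to 1/√C_h, and the implied cost ratios relative to the sedentary stratum are:

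- active: (54/43)² = 1.58
- athletes: (54/33)² = 2.68

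This agrees with the stated order C3 > C2 > C1. The split is compatible with the formula but says nothing about selection.

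**3. Activity level and source.** In the table each IPAQ-SF category matches exactly one route. As written, a highly active person without a club, or a moderately active person who is not a trainer, has no way in. Activity and source therefore do not vary independently, and their effects cannot be separated.

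The 70/30 split gives 0.7 × 130 = 91 for development and 0.3 × 130 = 39 for validation. Both parts come from the same three routes, so an equation that has absorbed a source effect will still predict well in the 39.

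**4. Illustration of size.** The documents give no figure for selection bias, so the shift is an assumption. Suppose self-selection shifts a mean, such as the mean difference between equation and DXA, by b standard deviations. With standard error SD/√n, a nominal 95% interval covers the population value with probability Φ(1.96 − b√n) − Φ(−1.96 − b√n).

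| Assumed b (SD) | b√130 | Coverage, n = 130 | b√39 | Coverage, n = 39 |
|---|---|---|---|---|
| 0 | 0 | 95% | 0 | 95% |
| 0.1 | 1.14 | 79% | 0.62 | 90% |
| 0.2 | 2.28 | 37% | 1.25 | 76% |
| 0.3 | 3.42 | 7% | 1.87 | 53% |

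A larger sample of the same kind makes coverage worse, because the interval narrows around the shifted value.

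**The case against.** The strongest reply is that the aim is to validate and build prediction equations, not to estimate a population mean. A regression relation can hold outside the sample if the model is right and the predictors capture what differs between populations, and design weights are then not needed. This stands. A reader might infer that the sample supports no generalisation at all, and that goes too far: what fails is inference resting on the sampling design. The protocol, however, states no model-based argument and relies on the label.

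Four further points also limit the concern:

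- **The split is not arbitrary.** It comes from a stated cost and variance formula. Unequal allocation is a legitimate design choice, and the missing inputs are normal for a condensed article.
- **Activity level is more than recruitment source.** A reader might treat the two as the same thing. IPAQ-SF category is an eligibility criterion and is measured on each person, so it is confounded with source, not identical to it.
- **Activity may not be selected.** Section 3 expects the ratios of body mass to waist girth and of waist girth to stature in the best model. The harm from an activity coefficient is conditional.
- **No pooled distortion can be calculated.** A reader might infer that the 25.4% share of athletes biases the pooled relative fat mass results by a calculable amount. Section 2.5.3 applies that equation to sedentary and active participants only, while 2.8 speaks of the total sample. Unless these are reconciled, it is unclear whether athletes enter that analysis.

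The full protocol might describe a random draw from trainer or club lists. That would not repair the open-call stratum, nor make the chosen institutions a random selection.

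**Conclusion.** The concern holds in this form: the Abstract and 2.7 state probability sampling, while 2.3 describes stratified recruitment of volunteers through selected institutions. The contradiction is internal to the article and needs no outside assumption. It is certain for 54 of the 130 participants, and nothing described supports the label for the other 76 (43 + 33).

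Design-based inference to the Colombian population, as framed in 1.2 and the Conclusions, is not supported. Geography is a second barrier: even a true probability sample here would reach only Medellín and its metropolitan area. Any wider use of the equations rests on model assumptions that should be stated.

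An activity coefficient, if one is selected, would be confounded with recruitment source, and the 91/39 split would not show it. The coverage figures are illustrative, resting on assumed shifts of 0.1 to 0.3 SD and a normal approximation. The total of 130 and its arithmetic are not affected.

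**What to change.** 1. In the Abstract and 2.7, replace the probability-sampling label with *stratified quota (non-probability) sample of volunteers*. The allocation formula can stay as the rule for stratum sizes.
2. In 1.2 and the Conclusions, limit the claim to healthy adults aged 18 to 59 from these source groups in the Medellín area. Say that wider use depends on model assumptions and on further validation elsewhere.
3. Add selection bias to 2.6.
4. In 2.8, report agreement statistics by stratum next to any pooled figure.
5. If activity level enters the selected equation, state that its effect is confounded with recruitment source, and also give the best equation without it.

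Items 1 to 3 are changes of wording. Items 4 and 5 add a few table rows and one further model from candidates already planned. Recruitment and sample size do not change. The price is a narrower claim, and stratum estimates from 33 to 54 people, or fewer in the validation part, will be imprecise.

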### 2.8. Statistical Methods

The descriptive analysis of the anthropometric characteristics of the study population will be reported as means, standard deviations, and 95% confidence intervals. First, the total sample of participants will be used for the external validation of the RFM (to estimate whole-body-fat percentage) [26] and the Takai et al., equation (to estimate fat-free mass) [35]. A correlation analysis will be performed by calculating Pearson’s r, intraclass correlation coefficient (ICC), concordance correlation coefficient (ρ_c_), adjusted coefficient of determination (aR^2^), and root mean squared error (RMSE) as compared to DXA measurements. Smaller values of standard error of the estimate (SEE) and RMSE will indicate that the estimated values are closer to the DXA measurements. Bland–Altman diagrams will be used for the concordance analysis. This is a procedure to determine whether two measurement methods, X and Y, agree sufficiently to be declared interchangeable (D = X − Y). The mean of these differences represents the systematic error (bias), while the variance of these differences (1.96 SD) measures the dispersion of the random error.

The development of the new equations to estimate fat mass (dependent variable) from different combinations of WG with sex, physical activity level, body mass, and stature (as predictor variables) will be carried out with multiple regression models under traditional (Ordinary Least Squares method) and Bayesian approaches (limited to three independent variables). For the latter, the ‘bayesbr’ and ‘bayes.lm’ R packages will be used. Variance inflation factors will be used to detect multicollinearity among predictors in the multiple linear regression models, and autocorrelation in the residuals will be assessed through the Durbin–Watson test. The variation explained by the model will be determined by the aR^2^. Finally, the SEE will be calculated for all generated models to measure the regression’s precision, while the RMSE will be used to evaluate how close the estimated values from each equation are to the actual measured values as reported elsewhere [42]. All possible regression models will be ranked using the akaike information criterion (AIC), the Bayesian information criterion (BIC), the Mallows’ C_p_, and the Hocking’s Sp. After compliance with all of the assumptions of the multiple regression analysis (normality of residual errors will be confirmed with the Omnibus k-squared and Jarque-Bera tests), the model with the better performance that includes WG will be selected for further analysis. The predictability of the equation in the selected model will be tested in the validation sample by calculating the aR^2^, RMSE, CCC, and ICC with its respective 95% CI. The concordance analysis will be performed by means of Bland–Altman diagrams, reporting the concordance intervals at 95%. Statistical tests will be carried out using the SPSS v26 statistical package (IBM Corp., Armonk, NY, USA) and the latest version of the environment for statistical computing R [54].

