Several authors have concluded that regression equations that use WG as a predictive variable appear to estimate body fat percentage more accurately [23,24,25]. In this sense, the relatively recent efforts of some research groups have developed equations that include WG as an independent variable to estimate fat mass and fat-free mass. On the one hand, Woolcott and Bergman [26] developed and validated a simple equation, named relative fat mass (RFM), to estimate the percentage of total body fat using the WG, stature, and sex of the American adult population (64 − (20 × (stature [m]/WG [m])) +  (12 × sex [0 for male and 1 for female])). The population data were extracted from the National Health and Nutrition Examination Survey (NHANES) between 1999 and 2006. The performance of RFM as an easy and useful tool in clinical practice, with a better correlation to DXA than BMI (RFM: R^2^ = 0.84; RMSE = 3.51% vs. BMI: R^2^ = 0.36; RMSE = 7.04%) has been validated in adults [27], children between 8 and 14 years old, and adolescents between 15 and 19 years old [28], obese subjects [29,30], and individuals with Down syndrome [31], among other populations at cardiovascular risk [32,33]. It is worth noting that the RFM defines obesity according to the cutoff points of the DXA measurements, to the point that following the rounded thresholds of the RFM baseline, the current recommendation for diagnosing obesity and predicting the risk of death with this parameter is 40% for women and 30% for men [34]. On the other hand, Takai et al. [35] developed an equation to estimate fat-free mass in male athletes using some indices as independent variables, including WG/body mass and stature/WG. The equation developed by these authors was validated with a sample of 48 athletes from different disciplines and showed a high correlation (R^2^ = 0.900, SEE = 2.3 kg [3.8%]) with the fat-free-mass data obtained by DXA (FFM (kg) = 0.883 × Body mass/WG [kg/m] + 43.674 × WG/Stature [cm/cm] − 41.480). The results of this study demonstrated that an equation using body mass and stature ratios with WG as independent variables is applicable and useful for predicting fat-free mass in male athletes.

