#### 2.5.3. Anthropometry-Based Analysis of Body Composition

We will estimate whole-body-fat percentage (as RFM) in sedentary and physically active individuals following procedures conducted by Woolcott and Bergman [26]. The Takai et al., equation [35] will be used to estimate fat-free mass in athletes. We will also report the sum of skinfolds (∑S) as an absolute variable (expressed in millimeters) which not only gives information about the local distribution of subcutaneous fat tissue, but which also indicates whole-body adiposity since it correlates with whole-body-fat mass [40,49]. As a musculoskeletal index, the skinfold-corrected muscle girths for arm, chest, waist, thigh, and calf will be calculated according to the expression: girth—(π × skinfold) [50].

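### Sections 2.5.3 and 2.8 give different validation populations for the two published equations, and neither deals with sex for the fat-free-mass equation, which was built in male athletes

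*Protocol article*

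**What the plan says.** Section 2.8 (Statistical Methods) opens the analysis of the first aim by stating that "the total sample of participants will be used for the external validation of the RFM (to estimate whole-body-fat percentage"), and the same sentence covers the FFM equation. It then lists Pearson's r, ICC, the concordance coefficient, adjusted R², RMSE and Bland–Altman diagrams against DXA.

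Section 2.5.3 assigns the equations differently. For RFM: "We will estimate whole-body-fat percentage (as RFM) in sedentary and physically active individuals". The FFM equation "will be used to estimate fat-free mass in athletes".

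On sex, section 1.1 reports that the authors of the FFM equation "developed an equation to estimate fat-free mass in male athletes using some indices as independent variables", and that a model of this form "is applicable and useful for predicting fat-free mass in male athletes". The equation is printed as "0.883 × Body mass/WG [kg/m] + 43.674 × WG/Stature [cm/cm] − 41.480", with no term for sex. RFM does have one: "12 × sex [0 for male and 1 for female"]. Section 2.3 enrols both sexes: "The study population will be healthy, male and female residents of Medellín". The sex composition of the strata is not given.

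**The concern.** External validation of the existing equations is one of the study's two aims, and the article fixes its population in two incompatible ways. If 2.5.3 is followed, no athlete has an RFM value and no non-athlete has an FFM value, so 2.8 cannot be carried out on the total sample. If 2.8 is followed, 2.5.3 is wrong.

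The second problem remains whichever section prevails. An equation without a sex term, derived in men, is to be compared with DXA in a study of men and women, and nothing restricts that comparison to men. If its error differs by sex, a pooled bias, RMSE, concordance coefficient and pair of limits of agreement depend on how many women happen to be recruited and may describe neither sex. Section 2.8 presents Bland–Altman analysis as the way to judge whether two methods are interchangeable, so the population chosen could decide the answer.

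**Working it through.** **1. Sample sizes (section 2.7).** The strata are 54 sedentary, 43 active and 33 athletes: 54 + 43 + 33 = 130, which reproduces the stated total.
- RFM: 130 under 2.8; 54 + 43 = 97 under 2.5.3.
- FFM equation: 130 under 2.8; 33 under 2.5.3, and fewer if only men count.

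**2. Formulas (section 1.1), with body mass BM in kg, waist WG and stature in m.**
- FFM equation = 0.883 × BM/WG + 43.674 × WG/stature − 41.480
- RFM (%) = 64 − 20 × stature/WG + 12 × sex (women 1, men 0)
- FFM implied by RFM = BM × (1 − RFM/100)
- Gap = FFM equation − FFM implied by RFM

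Unit check: the published SEE of 2.3 kg (3.8%) implies a mean FFM of 2.3/0.038 = 60.5 kg. For an assumed man of 80 kg, WG 0.88 m and 1.73 m, the equation gives 61.0 kg, so the units are read correctly.

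**3. Worked cases (body sizes are assumptions).**
- Woman, 60 kg, WG 0.75 m, 1.60 m: 70.64 + 20.47 − 41.48 = 49.6 kg. RFM = 76 − 42.67 = 33.3%, implied FFM 40.0 kg. Gap +9.6 kg.
- Female athlete, 57 kg, WG 0.69 m, 1.62 m: 72.94 + 18.60 − 41.48 = 50.1 kg. RFM 29.0%, implied FFM 40.4 kg. Gap +9.6 kg.
- Man, 70 kg, WG 0.80 m, 1.72 m: 77.26 + 20.31 − 41.48 = 56.1 kg. RFM 21.0%, implied FFM 55.3 kg. Gap +0.8 kg.

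Ten assumed female profiles (50–75 kg, WG 0.65–0.90 m, 1.55–1.65 m) give +8.9 to +12.0 kg. Six assumed male profiles (65–90 kg) give −0.3 to +1.4 kg.

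**4. Sensitivity to the benchmark.** Replace RFM by an assumed fat percentage:
- Female athlete above: 50.1 − 57 × 0.80 = +4.5 kg at 20% fat; +7.3 kg at 25%.
- Woman of 60 kg, WG 0.72 m, 1.60 m (FFM equation 51.8 kg): +3.8 kg at 20%, +6.8 at 25%, +9.8 at 30%, +12.8 at 35%.
- At 20% fat the gap also depends on the waist: with WG 0.75 m instead of 0.72 m, the 60 kg woman's gap is +1.6 kg.

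**5. The protocol's own reference (section 2.6).** DXA fat-free mass is reduced by (fat mass/0.85) × 0.15, which widens every gap by that amount.
- Woman of 60 kg, WG 0.75 m: fat mass 20.0 kg, subtraction 3.5 kg, gap 9.6 + 3.5 ≈ +13.2 kg.
- Man of 70 kg: fat mass 14.7 kg, subtraction 2.6 kg, gap 0.8 + 2.6 = +3.4 kg.
- Ranges: +11.4 to +17.4 kg in the ten women, +3.4 to +4.4 kg in the six men.

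**6. Effect of pooling.** Assume a within-sex SD of 2.3 kg (the published SEE) and a share p of women. Pooled bias = p × gap(women) + (1 − p) × gap(men); pooled SD = √(2.3² + p(1 − p) × difference²).
- After the section 2.6 adjustment, gaps 13.2 and 3.4 kg: bias 5.9, 8.3 and 10.8 kg at p = 25%, 50% and 75%. At 50%, SD = √(5.29 + 0.25 × 9.8²) = 5.4 kg and the limits are about −2.3 to +18.9 kg.
- Smaller contrast, female athlete at 20% fat: 4.5 + (11.4/0.85) × 0.15 = 6.5 kg, against 3.4 kg in men. At 50% the bias is 4.95 kg, SD = √(5.29 + 0.25 × 3.1²) = 2.8 kg and the limits are about −0.5 to +10.4 kg.

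**7. Precision of split results.** The 95% CI half-width around one limit of agreement is 1.96 × √(1/n + 1.96²/(2(n − 1))) SD: 0.59 SD for n = 33 and 0.83 SD for n = 17.

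**The case against.** The best defence is that the total sample means only the unsplit data: section 2.8 begins with it, and the 70/30 development/validation split applies to the new equations. Section 2.5.3 would then say which equation goes to which stratum. That is plausible, but it is not written, and the sentence as it stands covers all strata and both sexes. This reading also leaves women athletes unaddressed.

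Other objections stand and limit the point:
- A reader might infer a fixed plan to report pooled results only. Section 2.8 lists the statistics without saying so, and breakdowns by sex and stratum may be in a fuller document.
- A reader might conclude that the FFM equation is about 10 kg wrong in women. The documents give no such figure. The benchmark is RFM, itself under test, rather than DXA, and it is weakest for female athletes, to whom 2.5.3 does not apply RFM.
- A clearly two-peaked Bland–Altman plot is not assured. Two equal normal groups with SD 2.3 kg show two peaks only if their means differ by more than 4.6 kg; in the smaller contrast they differ by 3.1 kg.
- That non-athletes would distort the result is not shown; the calculation varies sex, not training status.
- Section 1.2 asks about validity across physical activity levels. Testing an equation outside its derivation group therefore falls within the aim, and poor performance there is a legitimate answer.

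**Conclusion.** The point holds as a contradiction plus an unhandled source of heterogeneity. RFM is to be validated in 130 or 97 people and the FFM equation in 130 or 33, and the sections must be reconciled. The sex problem applies under either reading if any women are among the people assessed. The article enrols both sexes but does not state the composition of the athlete stratum.

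The size is illustrative and rests on assumed body sizes. Before the section 2.6 adjustment, the gap to the RFM-implied value is about 9 to 12 kg in typical women and about −0.3 to +1.4 kg in men, falling to about 4 to 4.5 kg for the two lean female profiles at 20% fat. After the adjustment, the RFM-based gaps are about 11 to 17 kg in women and 3 to 4 kg in men. Most of these differences between the sexes exceed the published SEE of 2.3 kg.

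It might be inferred that restricting the analysis to men would give a clean validation, or that male athletes must be the sole primary group. Neither follows: the adjusted reference leaves a gap of about 3 to 4 kg in men too, and such a restriction would narrow the question in section 1.2.

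**What to change.** - Make 2.5.3 and 2.8 name the same prespecified validation population for each equation, before results are seen. If the total sample means only the data before the 70/30 split, say that.
- Report every agreement statistic and Bland–Altman plot separately by sex and by stratum.
- Label results outside an equation's derivation population as transportability: the FFM equation in women or non-athletes, and RFM in athletes if 2.5.3 stands.
- Do not base the validity conclusion on a single pooled estimate.

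The cost is wording and tabulation; recruitment and measurement are unchanged. The price is precision: the 95% CI around each limit of agreement has a half-width of about 0.6 SD with 33 people and about 0.8 SD with 17. Those intervals should be reported.

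### Section 2.8 counts a small SEE as closeness to DXA although SEE cannot register bias, and agreement indices pooled over sexes and activity groups can overstate agreement within them

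*Protocol article*

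**What the plan says.** All places are in the protocol article.

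- **Section 2.8, first paragraph (existing equations).** "the total sample of participants will be used for the external validation of the RFM" and of the published fat-free-mass equation. The indices are Pearson's r, "intraclass correlation coefficient (ICC), concordance correlation coefficient", and "adjusted coefficient of determination (aR^2^), and root mean squared error (RMSE) as compared to DXA measurements". The reading rule follows: "Smaller values of standard error of the estimate (SEE) and RMSE will indicate that the estimated values are closer to the DXA measurements". After that, "Bland–Altman diagrams will be used for the concordance analysis", with the mean difference defined as the systematic error.
- **Section 2.8, second paragraph (new equation).** SEE is given the job of measuring the regression's precision, and RMSE the job of showing how near estimates lie to measured values. The chosen equation "will be tested in the validation sample by calculating the aR^2^, RMSE, CCC, and ICC", again with Bland–Altman diagrams. SEE and r are not on this list.
- **Section 2.5.3.** RFM is applied to sedentary and active people and the fat-free-mass equation to athletes. This does not match the total sample of section 2.8.
- **Sections 2.3 and 2.7.** Both sexes are enrolled, in strata of 54, 43 and 33, with a 70/30 development/validation ratio.
- **Section 2.6.** The DXA fat-free-mass reference is lowered by the fat-free part of adipose tissue (FFAT), calculated as 0.15 × fat mass ÷ 0.85.

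**The concern.** An external validation asks whether the published coefficients, used as they stand, reproduce DXA in this population. SEE answers a different question: how tightly DXA scatters around a line refitted in the new data. An equation that reads several points too high throughout can have an excellent SEE, so a reader who applies the stated rule would count that as evidence of closeness.

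The second issue is pooling. Correlation-type indices rise with the range of the data, and this study deliberately combines men and women and three contrasting activity groups. Section 1.2 asks about validity across activity levels. A pooled index, or a pooled mean bias, can look good while the answer differs between groups.

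**Working it through.** **1. SEE and bias.** Replace the estimate x by a + b·x. Regressing DXA on a + b·x gives the same fitted values and residuals as regressing DXA on x, so SEE, r² and a refitted aR² do not change. RMSE on estimate minus DXA does: for a constant bias, RMSE² = (SD of differences)² + bias².

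**2. Size.** Simulation with 600 runs, strata 54/43/33 (section 2.7), outcome fat %. Assumed, not in the documents: half of each stratum male, within-cell SD 5, error SD 3.5, 6 points between successive activity groups, 10 points between sexes.

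| Constant bias (points) | 0 | 3 | 5 | 8 |
|---|---|---|---|---|
| r | 0.93 | 0.93 | 0.93 | 0.93 |
| aR² (refitted) | 0.86 | 0.86 | 0.86 | 0.86 |
| SEE | 3.2 | 3.2 | 3.2 | 3.2 |
| ICC, consistency | 0.92 | 0.92 | 0.92 | 0.92 |
| RMSE | 3.5 | 4.6 | 6.1 | 8.7 |
| Bland–Altman mean | 0 | 3 | 5 | 8 |
| CCC and ICC, absolute agreement | 0.92 | 0.87 | 0.80 | 0.66 |

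Analytic check from the RFM figures in section 1.1 (R² 0.84, RMSE 3.51). Taking RMSE = SD·√(1 − R²), SD = 3.51/√0.16 = 8.78. With equal SDs for estimate and DXA, CCC = √0.84 × 2SD²/(2SD² + bias²) = 0.92, 0.87, 0.79 and 0.65, which agrees with the table.

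**3. Why an offset is plausible here.** FFAT = 0.15/0.85 × fat mass = 0.176 × fat mass. Section 1.1 gives the fat-free-mass equation an SEE of 2.3 kg. Assume that the equation is centred on unadjusted DXA fat-free mass and treat the shift as constant:

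| Assumed fat mass (kg) | 10 | 15 | 20 | 25 |
|---|---|---|---|---|
| Shift of reference (kg) | 1.8 | 2.6 | 3.5 | 4.4 |
| √(2.3² + shift²) (kg) | 2.9 | 3.5 | 4.2 | 5.0 |

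SEE would stay at 2.3 kg. In practice fat mass varies between people, so SEE would pick up part of that variation, but not the common offset.

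**4. aR² in the validation sample.** If it comes from a refitted line, step 1 applies. If it is computed with coefficients held fixed, nothing was estimated in that sample and the degrees-of-freedom penalty has no basis. R² = 1 − SSE/SST with fixed coefficients avoids both problems.

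**5. Pooling.** With no bias and the error SD unchanged, CCC = 2V/(2V + 3.5²), where V is the variance of DXA fat %.

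- Within a cell, V = 25, so CCC = 50/62.25 = 0.80 (simulated mean over six small cells, 0.78).
- Pooled, sex adds (10/2)² = 25 and activity adds 23.15 (steps of 6 weighted 54/43/33). V = 73.15, so CCC = 146.3/158.55 = 0.92.
- With smaller differences (3 and 6 points), pooled CCC is 0.87. With none it is 0.80.
- If the equation tracks DXA weakly within cells (slope 0.3), simulated CCC is 0.82 pooled against 0.35 within.

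Individual error is the same pooled or within in the first three cases. Only the range differs.

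**6. Cancelling biases.** Stratum biases of −3, 0 and +4.9 give a pooled bias of (54 × −3 + 43 × 0 + 33 × 4.9)/130 = −0.3/130 ≈ 0.0. The variance of differences becomes 3.5² + (54 × 9 + 33 × 24.01)/130 = 12.25 + 9.83 = 22.08, so SD is 4.70 and the limits are about ±9.2, against ±6.8 without group bias. Simulated pooled CCC is 0.84 and RMSE 4.7.

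**7. Validation set.** 30% of 130 is 39, or about 16, 13 and 10 if split in proportion. At n = 10, r = 0.78 has a Fisher interval of tanh(1.045 ± 1.96/√7), about 0.30 to 0.95.

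**The case against.** A reader might infer that closeness will be judged from SEE, r and aR² alone, so that a badly calibrated equation would pass. The text does not support that. RMSE stands in the same sentence as SEE, r and aR² are listed as correlation indices and are not called measures of closeness, and Bland–Altman analysis with an explicit bias estimate follows, as does CCC among the listed indices. In step 2 each of these moves with a constant bias. For the new equation, SEE and r are not on the validation list at all. This objection stands and limits the point.

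A reader might also take the sex term of RFM, "12 × sex [0 for male and 1 for female", as a 12-point sex gap in body fat and conclude that sex alone explains half the variance. That coefficient is the difference at equal stature/WG. The actual gap also depends on how mean stature/WG differs between the sexes, which the documents do not give. The inflation from pooling therefore cannot be sized from that coefficient.

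Section 2.5.3 further suggests that pooling over all three strata may not be intended for the existing equations. That is fair, but RFM would still pool both sexes and two activity groups, and the two sections disagree. Finally, subgroup tables are a detail that a condensed article may leave to the full protocol. Their absence is not the fault raised here. The misassigned SEE is stated in the text, and the subgroup tables are the remedy for the limits of the pooled analysis.

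**Conclusion.** The point holds in a limited form and should be corrected, but it does not undermine the study.

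- **Certain, by algebra:** SEE is wrongly named as a sign of closeness to DXA for a fixed equation, and the first paragraph of section 2.8 conflicts with the second on what SEE is for.
- **Not supported:** that a constant overall bias would go unseen. The planned RMSE (on estimate minus DXA), mean difference and CCC would show it. ICC would do so only in its absolute-agreement form.
- **Certain in direction, assumed in size:** pooled r, ICC and CCC are raised by between-group spread. Pooled CCC ranged from 0.80 with no group differences to 0.92 with large ones, against 0.78 within cells. About 0.02 of that gap is a small-sample effect and not pooling.
- **Possible:** opposite stratum biases cancel in the pooled mean. The limits of agreement then widen, here from ±6.8 to ±9.2, so the signal is weakened but not lost.

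**What to change.** 1. Delete SEE from the closeness sentence in section 2.8. Judge closeness on RMSE computed on estimate minus DXA, mean bias, limits of agreement, CCC and absolute-agreement ICC. SEE can stay as a precision measure for fitted models.
2. In the validation sample, replace aR² with R² = 1 − SSE/SST, coefficients held fixed.
3. For the external validation of the existing equations, report bias, limits of agreement and RMSE by sex and by activity stratum alongside the pooled values. For the new equation's validation set of about 39, give these as supportive only.
4. Reconcile sections 2.5.3 and 2.8 on the groups in which each equation is validated.

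The cost is some rewording and a few extra tables. Subgroup intervals will be wider, and no further data are needed.
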